### Data analysis and management

Data will be analysed using IBM SPSS 26.0 (SPSS Inc., Chicago, IL). At first, a descriptive analysis will be conducted to identify outliers, distributions and to display the baseline characteristics of both groups (means, proportions, standard deviations). To evaluate the effects of the intervention, data of all patients will be processed, regardless of whether they fully received or dropped out of the intervention (intention-to-treat-analysis). Thereby, data will be analysed until the date of drop out. As a secondary analysis, only the data from the participants who participated at least 80% of the intervention will be included in a per-protocol analysis. Missing data will be imputed using multiple imputation, under the assumption that data are missing at random. Statistical significance level will be set at *p* ≤ 0.05 (1-sided).

In order to analyse differences between the groups at the time points post and follow-up, two ANCOVAs with baseline adjustments will be undertaken (covariates: baseline values and, when required, e.g. age, sex etc.) for all outcome measures. Subsequently, alpha-adjustments will be undertaken. In case the assumptions for the ANCOVA will be violated, mixed models will be used. To further elaborate the outcomes and their interactions, additional parametric or nonparametric statistical analyses will be applied. Exploratory mediation analysis will be performed supplementary.

To preserve the confidentiality, all participants will receive a specific code with which the data will be labelled, while the participants contact data will remain under lock. The collected data will be stored digitally and can only be accessed by the study group. Therefore, the data will be transmitted by one person and checked for correctness by another (transmission errors and plausibility). In this study, no data monitoring committee and interim analysis will be established, because of the minimal risks associated with the intervention. Overall, the data management will be in line with of the European General Data Protection Regulation.

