### Sample size

Sample size was calculated using G*Power (version 3.1.9.7.). Because previous studies have shown large effect sizes for changes in the TUG performance after single interventions (dancing [49], strength training [50]) as well as after multimodal interventions [51] in healthy older adults, a large effect size (f = 0.40) was assumed for the sample size calculation. Considering an α level of 0.05, a power of 0.95, two groups and two covariates (baseline scores and, when required, e.g. age, sex, etc.), the required total sample size for an analysis of covariance (ANCOVA) amounted 84 participants. With a hypothesized dropout rate of around 15%, a total sample size of 100 participants seems to be legitimated.

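### Cutting data at drop-out conflicts with the stated intention-to-treat rule and, if drop-out means stopping MultiMove, is liable to bias the primary TUG contrast

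*Protocol article*

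**What the plan says.** All statements are in the protocol article. Four sentences under Data analysis and management bear on the point:

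- Population: "data of all patients will be processed, regardless of whether they fully received or dropped out of the intervention (intention-to-treat-analysis").
- Cut-off, in the next sentence: "Thereby, data will be analysed until the date of drop out".
- Secondary analysis: "only the data from the participants who participated at least 80% of the intervention will be included in a per-protocol analysis".
- Missing data: "Missing data will be imputed using multiple imputation, under the assumption that data are missing at random".

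The model follows: "two ANCOVAs with baseline adjustments will be undertaken", one at post (t1) and one at follow-up (t2).

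Other sections set the context. Study design and setting and Table 3 place TUG at baseline, week 12–14 and week 24–26, with nothing in between. Study interventions gives MultiMove to the intervention group (IG) over 12 weeks; the control group (CG) may join only once its follow-up measurements are done. That section also has reasons recorded when someone ends MultiMove early. Study procedure provides a payment at follow-up to encourage completion of all measurements.

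**The concern.** Intention-to-treat means that a randomised patient's outcome counts whatever happened to the treatment. The population sentence says this. The cut-off sentence is tied to it by its opening word, and the only drop-out mentioned so far is drop-out from the intervention. Read that way, it takes back what the population sentence grants: the patient stays in the analysis set, but the values observed after stopping do not.

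The timing makes this consequential. The programme ends at about the time of the first post-baseline measurement, so a patient who stops in, say, week 6 has only a baseline value before that date. Both ANCOVA time points are lost. Before follow-up only the IG has MultiMove to stop, so on this reading the loss falls on one arm.

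At stake is the primary TUG contrast. It would move toward the question of what MultiMove does for those who keep attending, which the 80% per-protocol analysis already addresses. Two analysts who read the undefined term differently could also report different primary results.

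**Working it through.** **The plan's own figures.** The sample-size section states "a large effect size (f = 0.40) was assumed for the sample size calculation" and "Considering an α level of 0.05, a power of 0.95, two groups and two covariates". With numerator df 1, denominator df 84 − 2 − 2 = 80 and noncentrality 0.40² × 84 = 13.44, the F test at 0.05 has power 0.952, and 84 is the smallest total that reaches 0.95. Inflating for 15% dropout gives 84/0.85 = 98.8, so 99; the planned 100 is consistent. The point below changes neither number.

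**Inputs for the illustration**

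- Effect in those who stay: d = 2f = 0.80 SD (from the plan).
- q, the share of the IG that stops MultiMove: 0.15. The plan's 15% is overall dropout, so applying it to the IG is an assumption.
- e, the effect in those who stop: assumed, 0 to 0.8 SD.
- D, how much worse the prognosis of stoppers is after baseline adjustment: assumed, 0 to 0.5 SD.

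**Formulas**

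- All t1 values kept: 0.8 − q(0.8 − e).
- Values after stopping removed: 0.8 + qD. Randomisation balances prognosis over the whole IG, so removing a share q with prognosis worse by D lifts the remainder by qD.
- Difference: q(0.8 − e + D).

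**Results with q = 0.15 and e = 0**

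- All data: 0.8 × 0.85 = 0.68 SD.
- Cut, D = 0: 0.80 SD; difference 0.12 SD (0.12/0.68 ≈ 18%).
- Cut, D = 0.3: 0.845 SD; difference 0.165 SD (24%).
- Cut, D = 0.5: 0.875 SD; difference 0.195 SD (29%).

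For q from 0.10 to 0.20, the difference is 0.08 to 0.16 SD with D = 0, and 0.11 to 0.26 SD with D from 0.3 to 0.5. With e = 0.8 and D = 0 it is zero.

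**Does imputation repair the cut?** This was simulated with 50 per arm, baseline-adjusted ANCOVA, an assumed baseline–outcome correlation of 0.6, no other loss, and imputation from baseline and arm. Effects are in SD in favour of MultiMove:

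| IG stopping | Effect in stoppers | Stopping related to poor outcome | All data | Cut, complete case | Cut, then imputed |
|---|---|---|---|---|---|
| 15% | 0.8 | no | 0.794 | 0.794 | 0.794 |
| 15% | 0.4 | no | 0.740 | 0.806 | 0.806 |
| 15% | 0 | no | 0.670 | 0.799 | 0.799 |
| 15% | 0 | yes | 0.674 | 0.964 | 0.964 |
| 30% | 0 | no | 0.553 | 0.800 | 0.802 |
| 30% | 0 | yes | 0.556 | 1.074 | 1.076 |

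Imputation after the cut agrees with complete case to within 0.002 SD. The reason is structural: the cut leaves no post-baseline TUG value from anyone who stopped during the course, so the imputation learns only from those who stayed. The rows marked yes are a strong scenario: (0.964 − 0.799)/0.15 implies a prognosis gap of about 1.1 SD.

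**No true effect.** At 15% stopping related to outcome, the complete-case one-sided rejection rate is 0.15 to 0.24 against a nominal 0.05; at 30% it is 0.26 to 0.49. With stopping unrelated to outcome it stays near 0.05 (0.052 and 0.058). Rejection rates after imputation were not computed.

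**The case against.** The best defence is that drop-out means leaving the study. The sample-size section uses the word for loss across the whole sample, Study interventions uses a different expression for ending MultiMove early, and Study procedure aims at complete measurement. Nowhere does the article say that people who leave the classes stop being measured. On this reading the sentence says only that data gathered before departure are used; it applies to both arms and fits the imputation. This stands as a possible reading. It does not remove the need for a change, because the preceding sentence points the other way and the article does not settle the matter.

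Four stronger readings are tempting but not supported:

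- A reader might infer that the cut can act only on the MultiMove arm. That holds on one reading of an undefined term.
- A reader might infer that cutting and imputing contradict each other. They do not: values removed by the cut could then be imputed. The conflict is between the cut and the intention-to-treat label.
- A reader might call the primary analysis a completer analysis. Formally it is not, since all randomised patients remain in the model. Only the estimate coincides, and that was shown for imputation from baseline and arm. The article does not state the imputation model, which may properly be left to the analysis plan.
- A reader might take the bias as established. It requires stoppers to benefit less or to have a worse prognosis, and the article gives no figure for either. Of the 0.165 to 0.195 SD obtained with a prognosis gap, 0.12 SD comes solely from assuming that stoppers gain nothing, which is severe for people who attended part of the course.

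**Conclusion.** The point holds in a conditional form. The cut-off sentence conflicts with the intention-to-treat rule it follows. On its most natural reading it discards t1 and t2 TUG values observed after a participant stops MultiMove, and imputation from baseline and arm does not bring back what was lost. The primary contrast is then liable to bias, usually toward MultiMove: about 0.80 SD instead of 0.68 SD if 15% of the IG stop and gain nothing, more if stoppers also have a worse prognosis, and none if stopping is unrelated to outcome and stoppers benefit equally. Only the 0.8 SD derives from the plan; the share stopping, their response and their prognosis are assumptions. If drop-out means leaving the study, nothing is wrong beyond the wording.

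This is not detail left to an analysis plan. The article states a rule, and that rule governs the primary outcome. It should be settled before analysis.

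**What to change.** Delete the cut-off sentence, or restrict it to withdrawal of consent or loss to the study. In its place state that:

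1. participants who stop MultiMove are still invited to t1 and t2;
2. all data obtained are analysed in the randomised arm whatever the attendance;
3. multiple imputation is used only for values not obtained, with a sensitivity analysis for departures from missing at random (its details can sit in the analysis plan).

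The cost is wording, an invitation call to those who stop classes, and a possibly smaller effect estimate. The visits and the follow-up payment are already planned, and the sample size does not change. In the simulation with no benefit in stoppers and stopping unrelated to outcome, keeping all data lowered the one-sided rejection rate only from 0.999 to 0.995 at 15% stopping, and from 0.998 to 0.960 at 30%.

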The classes will start with the motor-cognitive component, which includes a warm-up phase with movements for all major muscle groups. The following motor-cognitive exercises are in line with a licensed concept (Life Kinetik®, [32]). Here, motor and cognitive tasks have to be performed simultaneously, requiring a redistribution of attentional resources. The exercises are designed in a way that they can hardly be executed without mistakes and the difficulty level will be adapted to the ability of the participants. During the following dance part, the participants will learn choreographies with increasing complexity over time, which will be adapted to their disability level. The choreographies will include different dance styles (e.g. Latin, Standard, Jazz) whereby each style focuses on a specific aspect, e.g. spatial orientation in Line dance or posture in Latin dance. To ensure that on the one hand different performance levels do not influence the dancing, but on the other hand, participants interact socially, the choreographies will be performed individually in a group setting and will be supplemented by dance formations. The final strength and flexibility training will focus on evidence-based exercises for the spine, back, abdominal and hip muscles [53].

The sessions will be supervised by two accredited instructors and will be conducted with a maximum of 15 participants. Instructors will keep an attendance list at each class. If participants are absent for two consecutive intervention sessions, they will be contacted by telephone. In order to improve attendance to MultiMove, participants of the IG will be asked to visit at least 80% of the classes. Moreover, participants will receive global information about the purpose and usefulness of the intervention at the first training session as well as specific explanations during the respective exercises. The individual perceived enjoyment of MultiMove will be assessed via the German version of the Physical Activity Enjoyment Scale once a week [54].

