Additionally, instructors will keep an activity log in each class to maintain intervention fidelity. Activity log will include a check-list with essential components of the intervention protocol and will be reviewed by an independent assessor. If participants will not be able to perform the planned exercises, because of the physical requirements, small individually adjusted modifications will be made and protocolled. Furthermore, if participants should premature terminate out of MultiMove, reasons will be recorded (e.g. personal reasons, relocation, illness that prevent physical activity or death).

The participants of the CG will be examined in the same time period as the IG receiving only the standard therapy (physiotherapy and drug-based pain management according to their individual needs), with the possibility to attend MultiMove as well, but not before the follow-up data collection is completed.

Besides, both groups will be asked not to start any (further) specific training intervention or pain treatment during the study period. Their physical activity level will be monitored by a questionnaire.

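### The 80% attendance rule for the secondary per-protocol analysis can select only intervention patients, so randomisation does not protect that comparison

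*Protocol article*

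**What the plan says.** The protocol article (Data analysis and management) makes intention-to-treat on all patients the main analysis. It adds a per-protocol analysis, labelled secondary, in which "only the data from the participants who participated at least 80% of the intervention will be included in a per-protocol analysis". It gives no criterion for controls. The stated ANCOVA adjustment is the baseline value and, when required, variables such as age and sex.

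Three statements under Study interventions decide how the rule can be applied:

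- The attendance target is set for one arm: "participants of the IG will be asked to visit at least 80% of the classes".
- Controls receive standard therapy only, "with the possibility to attend MultiMove as well, but not before the follow-up data collection is completed".
- Attendance is recorded: "Instructors will keep an attendance list at each class". No matching adherence measure for standard therapy is described.

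**The concern.** Attendance is observed after randomisation and in one arm only. If patients who attend most classes would have had better outcomes anyway, selecting them and keeping every control builds a difference into the comparison that MultiMove did not cause.

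The article gives some reason to expect such a link. It lists illness among the reasons for leaving the programme (Study interventions), names the physical ability to take part actively for 60 minutes as a limitation (Discussion), and connects fear of pain with lower activity and more disability (Background). Adjustment for the baseline value removes only the part of prognosis that this value captures.

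This is the only planned analysis aimed at patients who substantially received MultiMove. The Discussion foresees later project stages and uptake into care, so its result may be cited as the effect of actually taking part.

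**Working it through.** **The plan's own figure.** The per-protocol rule has no figure of its own. The sample size reproduces: noncentral F test with f = 0.40, α = 0.05, two groups and two covariates, so df2 = 84 − 2 − 2 = 80 and λ = 0.40² × 84 = 13.44. Power at N = 84 is 0.952, and 84 is the smallest N that reaches 0.95. Then 84/0.85 = 98.8, rounded in the plan to 100, or 50 per arm. This does not depend on the per-protocol rule.

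**Who can meet the rule.** Two sessions a week for 12 weeks give 24. Since 0.80 × 24 = 19.2, a patient needs at least 20. Controls have 0 of 24 in the analysed period. The threshold can therefore sort only the IG.

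**Illustrative bias with no true effect.** Assumptions, none of them from the article:

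- The outcome after baseline adjustment has SD 1, with higher values better.
- It has correlation r with a normally distributed tendency to attend.
- The top fraction p of the IG reaches 80%.
- All 50 controls are kept.

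Formulas:

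- c = Φ⁻¹(1 − p), m = φ(c)/p
- bias = r·m
- variance among attenders v = 1 + r²(c·m − m²)
- SE = √(v/(50p) + 1/50)
- one-sided error = Φ(bias/SE − 1.645)

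Example, p = 0.70 and r = 0.3: c = −0.524 and m = 0.497, so bias = 0.3 × 0.497 = 0.149. Next, v = 1 + 0.09 × (−0.260 − 0.247) = 0.954 and SE = √(0.954/35 + 0.02) = 0.217. The error is Φ(0.149/0.217 − 1.645) = 0.169. A simulation of 20,000 trials gave bias 0.152 and error 0.168.

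Each cell shows bias in SD, then one-sided error:

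| IG reaching 80% | r = 0.1 | r = 0.2 | r = 0.3 |
|---|---|---|---|
| 90% | 0.019; 6.1% | 0.039; 7.3% | 0.058; 8.7% |
| 80% | 0.035; 6.9% | 0.070; 9.5% | 0.105; 12.6% |
| 70% | 0.050; 7.8% | 0.099; 11.7% | 0.149; 16.9% |
| 60% | 0.064; 8.6% | 0.129; 13.9% | 0.193; 21.3% |

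At r = 0 the bias is zero and the error stays at 5%. With 42 per arm (84/2) before selection and 70% attenders, r = 0.2–0.3 gives bias 0.10–0.15 SD and error 11–15%.

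**The randomisation-based alternative.** Take 50 per arm and a binary exposure (attender or not, 70% attenders) that only the IG can have. The complier-average effect is then the intention-to-treat difference divided by 0.70.

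- Its SE is √(1/50 + 1/50)/0.70 = 0.20/0.70 = 0.286.
- The SE of the attenders-against-all-controls comparison, ignoring the small reduction in v, is √(1/35 + 1/50) = 0.220.
- The ratio is 0.286/0.220 = 1.30.

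Simulated at r = 0.3, the complier-average estimate had mean −0.007 with no effect and 0.797 when the true effect in attenders was 0.80. The attenders-only comparison gave 0.95 for the same true 0.80. These figures are for the binary exposure. They were not obtained for a 0–24 session count.

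**The case against.** Taken alone, the sentence could be read as removing every control, which would leave no comparator. The article does not support that as the intended analysis: the 80% target is addressed to the IG, and controls are barred from the classes. Read together, these passages make the rule a filter on the IG, and what is missing is an explicit sentence about controls.

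A reader might also infer that the analysis would show a benefit even if MultiMove did nothing. That is too strong. Over the illustrated range, about 79–94% of null trials would still give no significant benefit, and with no correlation there is no bias. The direction is itself an assumption. Exercises are adapted to ability, the listed reasons for stopping include relocation and personal reasons as well as illness, and baseline adjustment is already planned.

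The strongest defence is that any per-protocol set carries this risk, that the plan calls the analysis secondary, and that it nowhere claims freedom from selection bias. That limits the weight of the point but does not remove it. The rule is stated, its only workable form selects one arm, and no caution is attached.

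The alternative has limits too. Participants are told their allocation (Study procedure), and IG members who miss two consecutive sessions are telephoned (Study interventions). Assignment could therefore influence outcome other than through attendance.

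**Conclusion.** The point holds as a minor one about a secondary analysis. The per-protocol rule works only as a selection of IG patients on attendance after randomisation, set against unselected controls. The result can be biased towards benefit if attendance is related to prognosis beyond the baseline value. The illustrated size is about 0.02–0.19 SD, with a one-sided 0.05 error of about 6–21%. It rests on assumed attendance (60–90%), an assumed correlation (0.1–0.3) and 50 per arm before selection. The article supports neither a particular value in that range nor a non-zero correlation. The intention-to-treat conclusion and the sample size are unaffected.

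**What to change.** - State that the 80% rule applies to the IG and that all controls are kept. Label the resulting comparison descriptive and open to selection by attendance.
- Make the secondary estimate of the effect of receiving MultiMove a complier-average causal effect: two-stage least squares with randomised arm as instrument, attendance from the existing lists as exposure, and the baseline value as covariate. Controls have no access before follow-up, so non-compliance is one-sided and the method suits the design.
- State its assumptions. Assignment must act only through attendance, which needs comment because participants know their arm. With the 0–24 session count the effect is taken as linear in sessions. With a binary 80% exposure, attendance below the threshold is taken to have no effect.

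No new data are needed and the analysis effort is small. The price is precision: a standard error about 30% larger under the binary 70%-attender illustration. The estimate is also essentially the intention-to-treat effect rescaled, so it describes the effect among those who attended and should not be presented as an independent test of benefit.

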### Secondary objectives

To examine changes in the LBP specific disability (Oswestry Disability Index, ODI) and health-related quality of life (EQ-5D-5L) between groups and over time.To evaluate the specific physical changes induced by MultiMove (gait variability, flexibility, functional exercise capacity and leg extensor muscle power).To analyse if MultiMove induces changes in selected executive functions (inhibitory control, cognitive flexibility) and/or in the haemodynamic response in the PFC during dual task standing and walking in CLBP patients.To determine the potential long-term psychosocial effects (Kinesiophobia, pain coping strategies) provoked by MultiMove.

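### Significance is set at one-sided 0.05, but the sample size of 84 matches only a two-sided ANCOVA test at 0.05

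*Protocol article*

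**What the plan says.** **Sizing (Sample size).** The calculation was made in G*Power for an ANCOVA. The effect is given as "a large effect size (f = 0.40) was assumed for the sample size calculation". The remaining inputs are given as "Considering an α level of 0.05, a power of 0.95, two groups and two covariates", and the result is "the required total sample size for an analysis of covariance (ANCOVA) amounted 84 participants". This is raised to 100 for dropout of about 15%. The section does not say whether α is one-sided or two-sided.

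**Analysis (Data analysis and management).** Two baseline-adjusted ANCOVAs, one at post and one at follow-up, are planned for every outcome measure. The threshold reads "Statistical significance level will be set at *p* ≤ 0.05 (1-sided". No reason is given for a one-sided test. The same section announces alpha adjustments but names neither the method nor the family of tests.

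**Direction of effect.** The Abstract assumes that MultiMove improves the outcomes it lists, and the Background expects improvement in physical, physiological and cognitive measures. Study design and setting calls the trial a superiority trial. One of the Secondary objectives is worded without a direction: "To analyse if MultiMove induces changes in selected executive functions (inhibitory control, cognitive flexibility) and/or in the haemodynamic response in the PFC".

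**The concern.** A two-group ANCOVA F-test at 0.05 is a two-sided test. If the trial was sized on that test but judged at one-sided 0.05, the evidence needed to claim benefit is lower than the evidence the trial was sized to deliver. The primary superiority claim on TUG could then rest on a result that the sizing test would call non-significant.

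The one-sided threshold is also set for all outcomes. Where the article does not say which direction counts as improvement, a one-sided test has no defined side, and the side could be picked once the data are known.

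**Working it through.** **Inputs** (all from Sample size, except the last):
- Cohen's f = 0.40
- α = 0.05, number of sides not stated
- target power 0.95
- 2 groups, so numerator df = 1
- 2 covariates, so denominator df = N − 2 − 2 = N − 4
- analysis threshold: one-sided 0.05 (Data analysis and management)

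**Step 1: reproduce the plan's 84.** The noncentral F-test has noncentrality λ = f² × N = 0.16 × N. At N = 84, λ = 0.16 × 84 = 13.44 with 1 and 80 df.
- N = 83: power 0.9495
- N = 84: power 0.9517

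So 84 is exactly the smallest N that reaches 0.95 with a non-directional test at 0.05. The answer is 84 for any number of covariates from 0 to 3.

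**Step 2: try the one-sided threshold.** This uses the noncentral t with noncentrality f × √N and the same df.
- N = 69: power 0.9498
- N = 70: power 0.9523
- N = 84: power 0.977

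One-sided 0.05 would have required 70, not 84. One-sided 0.025, which is the same as two-sided 0.05 for a benefit, gives 84 again.

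**Step 3: size of the mismatch with 80 df.**

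| Rule | Significant in MultiMove's favour if | False-positive rate in that direction |
|---|---|---|
| F-test at 0.05 (sizing) | t > 1.990 | 0.025 |
| One-sided 0.05 (analysis) | t > 1.664 | 0.05 |

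The ratio is 0.05 / 0.025 = 2, per test and before any adjustment. Results with t between 1.664 and 1.990 (two-sided p between 0.10 and 0.05) pass the analysis rule and fail the sizing test.

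**Step 4: effect of an alpha adjustment.** The article gives no method, so a Bonferroni split over the two time points is assumed here.
- Starting from one-sided 0.05: 0.05 / 2 = 0.025 one-sided at each time point. This equals two-sided 0.05, so the gap in Step 3 closes. Power at 84 is 0.952.
- Starting from two-sided 0.05: 0.05 / 2 = 0.025 two-sided at each time point. Power at 84 is 0.914, and 98 analysed participants are needed for 0.95.

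**Step 5: power after alignment to two-sided 0.05, single unadjusted test.** It is 0.952 at 84, 0.954 at 85 (100 × 0.85) and 0.977 at 100. Dropout arithmetic: 84 / 0.85 = 98.8, so 99, consistent with the planned 100.

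**The case against.** **A prespecified one-sided test is a legitimate, disclosed choice in a superiority trial.** It can be. But the 84 was not computed for a one-sided test at 0.05, and no rationale links the two sections.

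**The sample size section never says two-sided.** Correct. Two-sidedness is inferred, and the inference rests on 84 being reproduced by that test and missed by 14 participants (84 − 70) with the other.

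**The alpha adjustments may remove the problem.** This stands in part. A Bonferroni split over the two ANCOVAs would bring each to one-sided 0.025, as Step 4 shows. A reader might infer that any TUG result with two-sided p between 0.05 and 0.10 would be announced as superiority; the article does not support that unconditionally. Equally, no method or family is named, so the adjustment cannot be relied on as a cure.

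**The direction is stated.** This largely stands. A reader might infer from the wording about changes that most outcomes have no direction. The assumed improvement in the Abstract and Background fixes the sign for TUG time and for measures such as the disability index, quality of life, kinesiophobia and the executive function tests. No sign is given only for the prefrontal haemodynamic response and, arguably, for some of the eight coping scores.

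**A one-sided test cannot declare worsening.** This adds little. Additional measurements provides a closing medical check-up for adverse events and a record of harms kept by the instructors, neither of which depends on the efficacy p-value.

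**Conclusion.** The inconsistency is real: the sizing and analysis sections use different tests. Before any adjustment, the false-positive rate in MultiMove's favour is 5% per test, where the sizing implies 2.5%.

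Two stronger readings are not supported. The overall type I error of each test is not doubled; it is nominally 5% under both rules, and only the share in the favourable direction doubles. Nor is the trial underpowered by the mismatch, since 84 exceeds the 70 that the stated one-sided test needs.

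The possibility of choosing the side afterwards is confined to the few secondary measures without a stated sign. It does not touch the primary outcome.

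The conclusion assumes that the sizing used the standard fixed-effects ANCOVA F-test with f = 0.40, which the exact match at 84 supports. The practical consequence for TUG depends on what the unspecified alpha adjustments turn out to be.

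**What to change.** 1. In Data analysis and management, replace the one-sided qualifier by two-sided 0.05 (equivalently one-sided 0.025), and report two-sided 95% confidence intervals.
2. State whether the alpha adjustment applies to TUG. If there is a single unadjusted primary TUG test, 84 participants and power 0.95 stand, as does the recruitment target of 100. If TUG is adjusted over both time points, attach that condition to the stated power: under the Bonferroni assumption, 0.914 at 84, with 98 analysed participants needed for 0.95. Allowing for the plan's 15% dropout, that is 98 / 0.85 = 115.3, so 116 randomised.

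Two-sided testing also removes the need to assign a side to the haemodynamic and coping measures.

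The first change costs one line and no extra participants. The second costs one sentence, and extra participants only if TUG is adjusted and power of 0.95 is kept.
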